### Power calculation

The primary study outcomes include two performance measures (cardiorespiratory fitness and muscle strength) and self-reported fatigue. It is expected that patients in the usual care condition will experience a 5%-10% decline in physical fitness during their chemotherapy treatment, that this will improve gradually during the post-treatment period, but will not necessarily return to pretreatment levels. It is hypothesized that the OnTrack program will yield at least a 20% improvement in general physical fitness. Based on the results of Courneya et al., a pretreatment mean for the 1-repetition maximum for leg extension is estimated to be 25 kg, with a standard deviation of 12 kg [15]. We expect that the Onco-Move program will help patients to maintain their pretreatment levels of cardiorespiratory fitness, but not necessarily improve, and that it will have little or no effect on muscle strength.

Based on the above figures, 100 patients per group are needed to detect a 0.40 standard deviation difference (Cohen's effect size [47]) in performance-based outcomes between the OnTrack group and the usual care group at the post-chemotherapy assessment, with power set at 0.80 and alpha at 0.05 (two-sided test).

We will recruit 360 patients into the trial to allow for an attrition of approximately 20% (i.e., patients who discontinue participation in the trial entirely, including failure to complete follow-up assessments). These numbers will be sufficient to detect a one-half standard deviation unit difference in self-reported fatigue. This magnitude of difference is generally considered to be indicative of clinically meaningful differences in patients' self-reported symptom experience [47,48].

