### Statistical analyses

All primary statistical analyses will be conducted on an intention-to-treat basis. Between group differences over time in performance indicators of general physical condition and muscle strength will be evaluated using multilevel regression analysis for % change from baseline, and two factor (group × time) multivariate analysis of variance with repeated measures on the time factor for comparison of mean scores. Scores on the self-report measures of fatigue, mood state and HRQoL will be calculated according to published scoring algorithms. Between-group differences over time in mean scores will be tested using a two factor (group × time) multivariate analysis of variance with repeated measures on the time factor. Effect sizes will be calculated using standard statistical procedures.

Supplementary analyses will be carried out in which data relating to compliance with the program elements are taken into account. Specifically, we will determine whether the level of compliance (based on attendance records and self-report data) is associated significantly with the changes over time in physical condition, muscle strength, fatigue, mood, and HRQoL. Similarly, we will investigate whether program effectiveness varies significantly as a function of patients' background characteristics, and particularly those variables assessing life style, health behavior and health attitudes.

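### Repeated-measures MANOVA, the only test named for fatigue and one of two unranked methods for fitness and strength, by default keeps only patients with all three visits and does not test the contrast used for sizing

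*Protocol article*

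**What the plan says.** All places are in the Methods of the protocol article.

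- **Study outcomes** sets three visits: before randomization (T0), end of chemotherapy (T1) and six-month follow-up (T2).
- **Statistical analyses** opens with "All primary statistical analyses will be conducted on an intention-to-treat basis". For the performance outcomes it then names two methods: a multilevel regression of percentage change from baseline, and a group-by-time "multivariate analysis of variance with repeated measures on the time factor for comparison of mean scores". Neither is called primary. For self-report outcomes, including fatigue, the group-by-time repeated-measures MANOVA is the only between-group test named.
- **Power calculation** states that "100 patients per group are needed to detect a 0.40 standard deviation difference" "in performance-based outcomes between the OnTrack group and the usual care group at the post-chemotherapy assessment", at 80% power and two-sided alpha 0.05. It recruits 360 patients "to allow for an attrition of approximately 20"%, and counts failure to complete follow-up assessments within that figure. For fatigue it gives a detectable difference of 0.50 SD, without naming a pair of arms or a visit.

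**The concern.** Two features of the MANOVA sit badly with the rest of the plan.

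First, in its standard form it analyses complete series only. A patient who attends T0 and T1 but not T2 contributes nothing, even to the T1 comparison. Observed data on a primary outcome would be set aside in an analysis described as intention-to-treat. That costs precision, and it can bias the T1 effect if the patients who leave after T1 differ between arms.

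Second, with three arms and three visits the interaction asks whether any arm's profile differs from any other's at any visit. The trial was sized for one pair of arms at one visit. A significant interaction does not say that OnTrack beats usual care at T1, and a non-significant one does not settle it either.

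For fitness and strength there is a further problem. Two methods on two scales, unranked, leave open which result counts.

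**Working it through.** **Inputs from the article:** d = 0.40 SD (performance) and 0.50 SD (fatigue); two-sided alpha 0.05; power 0.80; 100 per group; 360 recruited; about 20% attrition; three arms; three visits. **Assumed:** equal allocation (120 per arm), equal correlation r between visits (0.3, 0.5 or 0.7), the arm means shown below, and the dropout mechanisms. The article gives none of these. The MANOVA is read as applied to one outcome at a time.

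**1. The plan's own figure.** n = 2(1.960 + 0.842)²/0.40² = 98.1, so 99 per group; the t-test version gives 99.1, so 100. The stated 100 is reproduced.

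**2. Complete cases at the plan's own loss.** 120 × 0.80 = 96 per group. Power = Φ(d√(n/2) − 1.96):

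- 96 per group, 0.40 SD: Φ(2.771 − 1.960) = 0.79
- 96 per group, 0.50 SD: Φ(3.464 − 1.960) = 0.93
- 120 per group, 0.40 SD: Φ(3.098 − 1.960) = 0.87

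If all the loss fell between T1 and T2, discarding the T1 values of those patients would take the unadjusted T1 contrast from 0.87 to 0.79. If the loss fell before T1, no analysis of observed outcomes would recover it.

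**3. Bias in the T1 change contrast among completers.** True effect 0.40 SD, 20% of each arm missing T2. Where loss depends on T1, the log-odds of loss fall by 1 per SD of T1 (rise by 1 where high values are lost).

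| Dependence of T2 loss on T1 | r = 0.5 | r = 0.7 |
|---|---|---|
| Same in both arms | 0.40 | 0.40 |
| Usual care only, low values lost | 0.32 | 0.35 |
| OnTrack only, low values lost | 0.49 | 0.45 |
| Opposite directions (low lost in usual care, high lost in OnTrack) | 0.23 | 0.29 |

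Varying the slope from 0.5 to 1.5 in the usual-care-only case gives 0.29 to 0.36 (r = 0.5) and 0.33 to 0.37 (r = 0.7). One-arm scenarios therefore span about 0.29 to 0.49 SD. As a check, selection that moves the completers' T1 mean by s moves the change contrast by (1 − r)s. The usual-care-only row gives s = (0.400 − 0.315)/0.5 = 0.17 and (0.401 − 0.349)/0.3 = 0.17, which agree. In these scenarios loss depends only on an observed T1 value, so a likelihood-based model that keeps those values is not biased by it.

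**4. What the interaction tests.** On the two differences T1 − T0 and T2 − T0 in three groups, Wilks' Λ gives F = [(1 − √Λ)/√Λ] × (N − 3 − 1)/2, with 4 and 2(N − 4) df; for N = 288, 4 and 568. Simulated power (3,000 runs, 96 per group, OnTrack minus usual care = 0.40 SD at T1):

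| Test and assumed means | r = 0.3 | r = 0.5 | r = 0.7 |
|---|---|---|---|
| Interaction: Onco-Move = usual care, effect gone at T2 | 0.69 | 0.85 | 0.98 |
| Interaction: Onco-Move = usual care, effect kept at T2 | 0.69 | 0.85 | 0.98 |
| Interaction: Onco-Move midway, effects halved at T2 | 0.43 | 0.59 | 0.82 |
| Interaction: Onco-Move midway, effects kept at T2 | 0.55 | 0.72 | 0.93 |
| T1 contrast, unadjusted | 0.79 | 0.79 | 0.79 |
| T1 contrast, baseline-adjusted (about) | 0.81 | 0.89 | 0.97 |

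The unadjusted row is the formula value from step 2, which the simulation matched within its error. If OnTrack and usual care are identical throughout and only Onco-Move dips by 0.40 SD at T1 (r = 0.5), the interaction rejects in 84% of runs and the T1 contrast in 5%. The two tests address different hypotheses.

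**The case against.** The strongest reply is that the article condenses a fuller plan. Complete-case deletion is the method's default, not a rule the article states. Imputation and follow-up contrasts may be set out in a full protocol or analysis plan that is not shown. This stands as a limit: the absence of a missing-data section is not the point here. The point is the test that the article does name, whose standard form is a poor match to the intention-to-treat statement and to the sizing.

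Four stronger readings are tempting, and the article does not support them.

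- *MANOVA is the primary test throughout.* It is not. For fitness and strength, on which the 0.40 SD sizing rests, multilevel regression is named first and can keep a patient without T2, although a percentage-change outcome still needs a baseline and one follow-up value.
- *The trial is badly underpowered.* A reader might compound 15% missing T1 with an independent 20% missing T2 (120 × 0.85 × 0.80 = 82 per group, power 0.72). The plan's 20% already includes missed follow-up assessments and describes patients who leave entirely. At that rate 96 per group remain, with power 0.79 at 0.40 SD and 0.93 at the fatigue target.
- *The effect will be diluted.* The bias can go either way, and it vanishes if loss depends on T1 equally in both arms at the same overall rate. Nothing in the article shows which mechanism will hold.
- *The omnibus test is always weaker.* It is not. At r = 0.7 its power is 0.82 to 0.98, above the unadjusted contrast. Part of the adjusted contrast's advantage comes from using the baseline value, not from dropping the omnibus test.

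It is also fair to say that a group-by-time test is not foreign to the aims, since the Background states hypotheses across three arms and two follow-up times. But those hypotheses name pairs of arms, some at a given time, and the interaction answers none of them directly.

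**Conclusion.** The point holds in this form. For fatigue, the only test named defaults to patients with all three visits. For fitness and strength, it is one of two methods with neither designated primary. With about 20% loss expected, that fits poorly with an intention-to-treat analysis and sets aside T1 data that were collected. It does not prove that the final analysis will be completers-only.

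The cost in precision is at most a fall from 0.87 to 0.79 in power for 0.40 SD, if all loss comes after T1. Bias is possible but not certain: about 0.29 to 0.49 SD for a true 0.40 SD when loss depends on T1 in one arm only, and further off (0.23 to 0.29) if the arms run in opposite directions. These figures rest on assumed correlations and dropout mechanisms.

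The mismatch of hypothesis does not depend on those assumptions: a 4-df interaction is not the difference "between the OnTrack group and the usual care group at the post-chemotherapy assessment". Whether it has less or more power depends on the visit correlation and on the Onco-Move and T2 means.

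**What to change.** For each primary outcome, replace the MANOVA, and the unranked pair of methods for the performance outcomes, with one likelihood-based linear mixed model:

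- T1 and T2 values as outcomes; baseline value, group, visit and group-by-visit as fixed effects; unstructured covariance; fitted by REML.
- All randomised patients with any post-baseline value, analysed in the arm assigned. Patients with no post-baseline value are still outside this model, so their number should be reported by arm.
- OnTrack versus usual care at T1 named as the primary contrast; the other pairwise and six-month contrasts estimated from the same model.
- The missing-at-random assumption stated, with one missing-not-at-random sensitivity analysis that allows the departure to differ by arm.

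Percentage change can be kept as a descriptive summary. The change is to the wording of the analysis section. It needs no new data or visits, and multilevel modelling is already planned for the performance outcomes. The only downside is slightly more analysis work.

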### Study outcomes

All study outcomes, with the exception of return to work, compliance and satisfaction with the interventions, are assessed prior to randomization (T0), at the completion of chemotherapy (T1), and at 6 month follow-up (T2). Return to work is assessed at T1 and T2, while compliance and satisfaction are assessed at T1 only, and only in the two intervention groups.

To facilitate comparison of results across the A-CaRe studies, the outcome measures used in these four clinical trials have been harmonized to as great an extent as possible.

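### The named group × time test for fatigue most naturally compares change from T0; adjusting for the T0 score would be more precise at almost no cost

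*Protocol article*

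**What the plan says.** The Statistical analyses section handles the self-report scales (fatigue, mood state, HRQoL) with a single method: "Between-group differences over time in mean scores will be tested using a two factor (group × time) multivariate analysis of variance with repeated measures". No other test is named for them. For the performance outcomes the same analysis of mean scores appears as the second of two methods: "multilevel regression analysis for % change from baseline, and two factor (group × time) multivariate analysis of variance with repeated measures on the time factor".

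Under Study outcomes, nearly all outcomes "are assessed prior to randomization (T0), at the completion of chemotherapy (T1), and at 6 month follow-up (T2"). Fatigue is primary: "The primary study outcomes include two performance measures (cardiorespiratory fitness and muscle strength) and self-reported fatigue".

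The Power calculation section states that "100 patients per group are needed to detect a 0.40 standard deviation difference" in performance outcomes between OnTrack and usual care after chemotherapy, "with power set at 0.80 and alpha at 0.05 (two-sided test"). On fatigue it adds: "These numbers will be sufficient to detect a one-half standard deviation unit difference in self-reported fatigue".

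**The concern.** If T0 is a level of the repeated factor, the pre-randomization score is treated as one more outcome. The group × time interaction then asks whether the groups differ in change from T0. That fixes the coefficient on the baseline score at 1 instead of estimating it, and makes no use of the fact that randomization gives the groups equal expected T0 means. The group main effect of the same model is no remedy, because it averages in T0, where the expected difference is zero.

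At stake is precision: intervals for a primary outcome, and for mood and HRQoL, would be wider than the collected data require. This is a separate matter from the percent-change scale and from missing visits. It remains with complete data on the raw score.

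**Working it through.** **Inputs.** From Power calculation: 0.40 SD (performance), 0.50 SD (fatigue), power 0.80, two-sided alpha 0.05, 360 patients, about 20% attrition. From Study outcomes: T0, T1, T2. Assumed: equal allocation, so 360/3 × 0.80 = 96 per group; one pairwise contrast at T1; equal SDs at T0 and T1; rho as a range, because the article gives none.

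**Reproducing the plan's figure.** For two post-treatment means, n = 2(1.960 + 0.842)²/0.40² = 98.1, so 99 per group, which agrees with the stated 100. For 0.50 SD the same formula gives 62.8, so 63. The figure of 100 is therefore matched by a plain two-group comparison with no baseline term.

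**Variance of one T1 score, in units of SD².**
- Post-treatment score alone: 1
- Change score: 2(1 − rho)
- T0 score as covariate: 1 − rho²
- Adjusted divided by change: (1 − rho²)/[2(1 − rho)] = (1 + rho)/2

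The ratio is below 1 for every rho below 1. Change equals post-only at rho 0.5 and is worse below that.

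**Power.** Noncentral t with 96 per group. The effective difference is delta/√[2(1 − rho)] for change and delta/√(1 − rho²) for adjustment, with one degree of freedom deducted for the covariate. Post-only power is 93% at 0.50 SD and 79% at 0.40 SD.

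| rho | (1+rho)/2 | 0.50 SD: change | 0.50 SD: adjusted | 0.40 SD: change | 0.40 SD: adjusted |
|---|---|---|---|---|---|
| 0.3 | 0.65 | 83.0% | 95.1% | 64.4% | 82.4% |
| 0.4 | 0.70 | 88.2% | 96.4% | 71.1% | 85.3% |
| 0.5 | 0.75 | 93.1% | 97.8% | 78.7% | 88.9% |
| 0.7 | 0.85 | 99.4% | 99.8% | 94.5% | 97.1% |

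A simulation of 20,000 trials at rho 0.5 and 0.50 SD gave 93.2% (change) and 97.7% (adjusted).

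**Where the fatigue statement would fail.** Setting change-score power for 0.50 SD to 80% and solving for rho gives about 0.24.

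**Three visits.** With T0, T1 and T2 the interaction is the joint test on T1 − T0 and T2 − T0. For two groups, equal correlations between visits and 0.50 SD at both follow-ups, its power against the baseline-adjusted joint test is 86% against 99% at rho 0.3 and 95% against 99.5% at rho 0.5.

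**Unequal SDs.** At rho 0.5, let the T0 SD be k times the T1 SD. The change variance is 1 + k² − 2(0.5)k: 0.84 at k = 0.8 and 1.24 at k = 1.2. Change-score power for 0.50 SD is then 96.4% and 87.2%. Adjusted power stays at 97.8%.

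**The case against.** **T0 as a level is inferred.** The article does not list the levels of the time factor, and a condensed article may leave covariates to the SAP. The first part stands, and the point is worded accordingly. It rests on the model that is named, not on the absence of a covariate. The alternative reading does not rescue the plan either: if T0 were not a level, the named test would not use the baseline score at all, which is also less efficient than adjusting for it.

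**Nothing stated is shown to be false.** This stands. A reader might infer that the fatigue test is biased, or that the trial is underpowered for fatigue. Neither follows. Randomization makes the change-score comparison unbiased, and the claim about 0.50 SD survives at 80% power for any rho above about 0.24.

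**A low rho has no source.** It is tempting to argue that chemotherapy between T0 and T1 must weaken the correlation. The documents give no correlation, so that remains conjecture. At rho 0.5 the fatigue gain is about 5 points, and at 0.7 it is under 1.

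**Performance outcomes have a second analysis.** This also stands. Percent change by multilevel regression is named alongside the mean-score test, and the Power calculation section does not say which was sized. A claim that the 0.40 SD sizing fails is therefore not supported. The mean-score test falls below a post-only comparison only if rho is below 0.5.

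**The figures simplify the plan.** The trial has three groups and three visits, and the MFI has five scales. The joint-test figures above show the same direction, but the exact size depends on the correlations, the SDs and the pattern of effect.

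**Conclusion.** The point holds as an efficiency loss in a stated analysis; it is not an error of validity or of sample size. Read with the assessment schedule, the only test named for fatigue, mood and HRQoL compares change from T0, and adjustment for the T0 score would be more precise at every rho below 1, apart from the trivial loss of degrees of freedom. For a 0.50 SD fatigue difference the gain is about 12 percentage points at rho 0.3, 5 at rho 0.5 and under 1 at rho 0.7. For mean performance scores at 0.40 SD it is about 10 points at rho 0.5.

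These sizes rest on 96 per group, a single pairwise T1 contrast, equal SDs and an assumed rho. That adjustment is preferable does not depend on the value of rho. It is best treated as a free improvement.

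**What to change.** In Statistical analyses, replace the group × time test for fatigue, mood and HRQoL by a model with T1 and T2 scores as outcomes and these terms: group, visit, group × visit, the T0 score of the same scale, and T0 score × visit. Alternatively, keep T0 as an outcome and constrain the group means to be equal there. Report the adjusted group contrasts at T1 and at T2. State explicitly which visits are outcomes and how T0 enters.

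The same change can be made to the mean-score analysis of performance.

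The cost is a change of wording and one or two degrees of freedom per model. The T0 scores are already being collected, so no further patients, visits or measurements are needed.

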### Cost-effectiveness analysis

This study also includes both incremental cost-effectiveness and cost-utility analyses. The cost-effectiveness ratio is calculated by dividing the difference between the mean total costs of the exercise and control groups by the difference in mean primary clinical effects of the groups [49]. In this analysis both direct and indirect costs will be taken into account. The incremental cost-utility ratio expresses the additional costs of the intervention per quality-adjusted life year (QALY) gained, compared to the usual care control group.

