We hypothesize that patients who undergo the Onco-Move or the OnTrack program will achieve better physical fitness levels, as assessed by objective performance tests, will report less fatigue, less mood disturbance, higher levels of physical activity and functioning in daily life, and better HRQoL than patients in the usual care control group. Furthermore, we hypothesize that patients in the OnTrack program will achieve more muscle strength and achieve greater gains in cardiorespiratory fitness than patients who follow the Onco-Move program. No differences are expected between the two programs in self-reported outcomes during treatment. However, it is hypothesized that, at the six month follow-up, patients who participated in the OnTrack program will report less fatigue, and higher levels of physical activity and functioning than those who participated in the Onco-Move program or usual care control group. Finally, we hypothesize that the OnTrack and Onco-Move programs will lead to a reduction in health care costs, patient and family costs, and costs of production losses, resulting in an cost-effective intervention.

If demonstrated to be effective, the availability of such physical activity and exercise intervention programs will be a welcome addition to the standard program of care offered to patients with cancer undergoing chemotherapy.

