## Methods

The present trial is one of four randomized controlled trials included in the Alpe d'HuZes Cancer Rehabilitation (A-CaRe) program. All studies within the A-CaRe program will evaluate the effectiveness and the cost-effectiveness of exercise-based rehabilitation interventions in different cancer patient and survivor groups. In the PACES study, patients are being randomized to one of three study arms. They will participate either in the Onco-Move or the OnTrack program, or will undergo usual care. The design of the trial and the anticipated flow of the participants are displayed graphically in Figure 1. The trial has been approved by the institutional review board of the Netherlands Cancer Institute (under number PTC 09.2711), as well as by the review boards of all hospitals from which patients are being recruited. This protocol follows the CONSORT guidelines [23]. Patient recruitment and data collection for this trial started in April, 2010.

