## Discussion

Compromised physical fitness and increasing fatigue are common side effects of cancer chemotherapy. Exercise during chemotherapy is a promising strategy for intervening at any earlier stage, to minimize or even prevent side effects both in the short- and long-term. Previous studies investigating the value of physical exercise during treatment have yielded inconsistent results, and many studies exhibited a range of methodological limitations.

In the current trial, we are evaluating the effectiveness and cost-effectiveness of a low intensity, home-based physical activity program, and a structured, supervised, moderate intensity exercise program in maintaining or enhancing physical fitness (cardiorespiratory fitness and muscle strength), in minimizing fatigue, and in enhancing HRQoL of patients undergoing adjuvant chemotherapy for breast cancer or colon cancer.

Our trial has several strengths, including: (1) the randomized trial design; (2) the multicenter nature of the trial; (3) the large sample size; (4) the relatively long-term follow-up; (5) the head-to-head comparison of two interventions varying in nature and intensity; (6) inclusion of both performance based and self-reported outcomes; (7) the use of intention-to-treat analysis; (8) the inclusion of a cost-effectiveness and cost-utility evaluation; and (9) the detailed evaluation of the background, attitudes and behavior of patients who decline to participate in the trial.

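### Both economic ratios are defined only against usual care, so they do not inform the choice between OnTrack and Onco-Move, and the hypothesised saving would make them negative

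*Protocol article*

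**What the plan says.** Cost-effectiveness analysis section: the economic part is introduced with "This study also includes both incremental cost-effectiveness and cost-utility analyses". For cost-effectiveness, the article obtains its ratio from "dividing the difference between the mean total costs of the exercise and control groups by the difference in mean primary clinical effects". The cost-utility ratio "expresses the additional costs of the intervention per quality-adjusted life year (QALY) gained, compared to the usual care control group". These are the only two ratios defined. The exercise side is not broken down by programme, and the cost-utility sentence speaks of one intervention.

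Methods, opening paragraph: "In the PACES study, patients are being randomized to one of three study arms".

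Background, hypotheses: both programmes are expected to improve fitness, fatigue and quality of life relative to usual care, and it is also expected that "the OnTrack and Onco-Move programs will lead to a reduction in health care costs, patient and family costs, and costs of production losses".

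Discussion, list of strengths: "the head-to-head comparison of two interventions varying in nature and intensity" is one item. The cost-effectiveness and cost-utility evaluation is another.

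**The concern.** Two features of the stated method fit this trial poorly.

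First, three mutually exclusive options are compared, but usual care is the only comparator named. By the Interventions section, OnTrack contains much of what Onco-Move offers (daily activity at the same Borg level, a diary, the same staged behavioural method) and adds two supervised sessions a week. A payer choosing between them needs the extra cost and extra effect of OnTrack over Onco-Move, and no ratio is defined for that step. If the programmes were pooled into one exercise group, the contrast would disappear.

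Second, a ratio of differences reads as a price per unit of benefit only when both differences are positive. The investigators hypothesise a negative cost difference and a positive effect difference.

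At stake is what the economic evaluation can conclude. Costs are a secondary outcome, and randomisation, sample size and the primary clinical comparisons are unaffected.

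**Working it through.** **The plan's own figures.** The Cost-effectiveness analysis section gives no cost, QALY difference or willingness-to-pay value, so there is nothing to reproduce. The sample-size figures do not enter the point. All money and QALY values below are assumptions that show the mechanism over a range.

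**Notation.** dC and dE are a programme's differences from usual care in mean cost and mean QALYs. Ratio = dC/dE. Head-to-head ratio = (dC_OnTrack − dC_OncoMove)/(dE_OnTrack − dE_OncoMove). Net monetary benefit at willingness to pay λ is NMB = λ·dE − dC.

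**Step 1: comparator.** Assume Onco-Move dC = 200, dE = 0.02 and OnTrack dC = 1,000, dE = 0.05.

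- Onco-Move vs usual care: 200/0.02 = 10,000.
- OnTrack vs usual care: 1,000/0.05 = 20,000.
- Pooled exercise vs usual care, equal arms: 600/0.035 = 17,143.
- OnTrack vs Onco-Move: 800/0.03 = 26,667.

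At λ = 25,000, NMB for OnTrack is 1,250 − 1,000 = 250 and for Onco-Move 500 − 200 = 300. OnTrack is acceptable against usual care, yet Onco-Move has the higher net benefit. This holds for λ between 20,000 and 26,667. At λ = 30,000 the order reverses: OnTrack 1,500 − 1,000 = 500, Onco-Move 600 − 200 = 400, although OnTrack still has the less favourable ratio against usual care.

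Over a range of assumed costs (dE held at 0.02 and 0.05):

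| dC Onco-Move | dC OnTrack | Onco-Move vs usual care | OnTrack vs usual care | Pooled vs usual care | OnTrack vs Onco-Move |
|---|---|---|---|---|---|
| 200 | 800 | 10,000 | 16,000 | 14,286 | 20,000 |
| 200 | 1,000 | 10,000 | 20,000 | 17,143 | 26,667 |
| 200 | 1,500 | 10,000 | 30,000 | 24,286 | 43,333 |
| 100 | 2,000 | 5,000 | 40,000 | 30,000 | 63,333 |

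**Step 2: sign.** For any c and e, (−c)/(+e) = (+c)/(−e). This is an identity and does not depend on assumed inputs. With c = 500 and e = 0.02, both ratios are −25,000. At λ = 20,000 the first has NMB = 400 + 500 = 900 and the second −400 − 500 = −900.

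Nor do negative ratios order programmes that all save money and improve outcome (λ = 20,000):

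| dC | dE | Ratio | NMB |
|---|---|---|---|
| −500 | 0.02 | −25,000 | 900 |
| −1,000 | 0.05 | −20,000 | 2,000 |
| −500 | 0.05 | −10,000 | 1,500 |

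The best of the three has the middle ratio, so neither the most nor the least negative value marks it.

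**Step 3: precision of the added contrast.** With 360/3 = 120 per arm and a common variance s², the pooled contrast against usual care has variance s²(1/240 + 1/120) = s²/80. OnTrack versus Onco-Move has s²(1/120 + 1/120) = s²/60. Its standard error is √(80/60) = 1.15 times the pooled one.

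**The case against.** The section consists of a few sentences in a condensed article. Dominance rules, bootstrap intervals, acceptability curves and willingness-to-pay ranges commonly sit in a fuller plan. That stands: their absence here is not the finding, which concerns the comparator and the form of ratio that the text does state.

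A reader might infer that the plan reads its result as a single ratio and that this rule would pick the wrong programme. The document does not support that. It defines two quantities and sets no threshold, ranking or adoption rule. Nor does it exclude a head-to-head ratio, so one cannot say that it will never be computed. If the arms are kept separate, the head-to-head ratio follows by subtraction, as Step 1 shows. The text does not promise that separation, and it defines no such result.

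The comparator also has a defence. The economic hypothesis takes the two programmes together and states no cost-effectiveness difference between them. The Discussion lists the head-to-head comparison apart from the economic evaluation, and in its limitations describes the planned comparisons as being with the control group. Ratios against usual care are therefore legitimate for that hypothesis. They are incomplete for a choice among three options.

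On the sign, anyone who sees both differences knows the quadrant and can simply report a saving with a benefit. That is correct, and it is part of the remedy. It means leaving the ratio aside in the case that the investigators expect.

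Finally, one might object that the primary clinical effect in the denominator is not unique. The plural wording is compatible with one ratio per primary outcome, and preferring QALYs as the main effect is a matter of choice, so neither is pressed here.

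**Conclusion.** The point holds in a limited form. As defined, both ratios compare exercise with usual care only, and pooling is left open, so they do not inform the choice between OnTrack and Onco-Move. Under the hypothesised result the ratio is negative and has no meaning as cost per unit gained.

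The sign result is an identity and needs no assumption about size. The comparator result shows what can happen: in the assumed cases OnTrack's ratio against usual care runs from 16,000 to 40,000 while its ratio against Onco-Move runs from 20,000 to 63,333. Whether this would change a decision depends on costs, effects and a threshold that the article does not give. It is not evidence that the trial will favour the wrong programme. The change is worth making because it widens what the economic evaluation can conclude at almost no cost.

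**What to change.** In the Cost-effectiveness analysis section:

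1. State that OnTrack and Onco-Move are analysed separately.
2. Add the OnTrack versus Onco-Move increment as part of a full incremental comparison: order the three arms by cost, remove dominated options, and compare each remaining option with the next.
3. Where a cost difference or an effect difference is not positive, report incremental net monetary benefit over a range of willingness-to-pay values, or state dominance.
4. Keep the ratio as a descriptive figure where both differences are positive.

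No new data are needed, since the planned EQ-5D and monthly cost diaries suffice. The cost is a little more analysis and a head-to-head estimate less precise than a pooled contrast (standard error about 15% larger under the equal-arm assumption above).
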